#### Web-based educational modules

The education implementation strategy will consist of six 10- to 15-min web-based modules, a tip sheet with clinic-specific interpreter access and use information, and four 5-min booster modules, all delivered online, along with quarterly reports on interpreter use to the enrolled provider. Education aims to improve provider motivation and capability related to interpreter use, by increasing conceptual and technical knowledge, enhancing interpreter access skills, shifting beliefs about their own capabilities and the consequences of use or nonuse, and increasing the intention to use an interpreter.

The educational module content is based on Seattle Children’s Hospital’s rigorously developed in-person workshop series, CONNECTing Through Interpreters [49–52]. In partnership with the interactive Medical Training Resources (iMTR) group at the University of Washington (UW; depts.washington.edu/imtr/) and content experts including experienced interpreters and providers, we transformed the workshops into interactive web-based modules. Modules were pilot tested with 15 primary care providers (PCPs) and revised based on feedback. Module-assigned providers will view them at a time and place they choose. We will track when participants access and complete modules as a marker of engagement.

The *online modules* cover 5 topics: (1) importance and fundamentals of good communication (delivered in 2 modules), (2) importance of professional interpreter use and disparities for populations with language barriers, (3) how to use an interpreter effectively, (4) what to do when the interpreted encounter is not going well, and (5) remote interpreter use and system’s challenges. Each module is 10–15 min long with audio, visual, and video content, developed using best practices from adult learning theory. Providers will be prompted to view a new module each week until all have been viewed.

During months 3–6 post-randomization, 4 brief (5 min) *booster modules* will be released, reviewing crucial points from initial modules. Boosters have been found to support behavior change in other settings [87]. Weekly reminders will be sent until they are complete. Providers who complete all modules will be eligible for points for continuing medical education (CME) and/or Maintenance of Certification (MOC); these points must be earned to maintain medical licensure and board certification and thus provide incentive for completion.

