#### Mobile video interpreting access

The mobile video interpreting access strategy will provide access to mobile video interpreting, technical support, a tip sheet for mobile video interpreting use, and an extra charger, shock-resistant case, disposable antimicrobial sleeves, and a positioning stand to support clinical use of the provider’s own device, along with quarterly reports on the enrolled provider’s interpreter use. Mobile video interpreting-assigned providers can use a study-issued smartphone instead of their own. The mobile video interpreting strategy aims to improve provider motivation, capability, and opportunity related to interpreter use, by decreasing cognitive overload, enhancing interpreter access skills, shifting provider beliefs about capabilities and the consequences of interpreter use, reinforcing use via satisfaction, and altering the environmental context and resources to make access easier and use more rewarding (Table 2).

*Access to mobile video interpreting* is achieved by downloading the application (app) online and then entering an access code linked to a billing account; after being entered, the code is no longer visible. Access can thus be controlled by study staff. Study staff will download and orient providers to the app, demonstrate use, and answer questions. *Technical support* will be offered on demand. A *tip sheet* will be emailed that includes mobile video interpreting instructions and best practices.

Several interpretation vendors have similar apps that can be downloaded onto personal devices but are rarely used in this way. These apps are HIPAA compliant, use end-to-end encryption, and are accessed with one touch (i.e., no additional log in or passwords); no data is downloaded to the device.

*Feedback to enrolled providers* will be provided quarterly with both strategies, as a report of the percent of visits with patients who use a language other than English for which the provider used professional interpretation.

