#### Cost data

Administrative cost data collected from clinics will include costs associated with interpreter vendor invoices and contracts; interpreter-specific clinic hardware (e.g., dedicated speakerphones); wireless Internet; and educational module development, following recommendations for economic analysis in implementation science [91]. Provider-incurred time and costs will be collected via the final survey, including time spent on each strategy, excess data charges associated with mobile video interpreting use (if any), and wear or damage to personal devices. Study team time related to implementing each strategy (e.g., installing mobile video interpreting, reminder emails) will be tracked in real time, as they would be performed by clinic staff with real-world implementation. We do not expect changes in clinic visit length, based on time-motion studies of interpreted patient visits [92, 93].

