#### Aim 3: Determine the incremental cost-effectiveness from a healthcare organization perspective of each implementation strategy (mobile video interpreting, education, and both)

We hypothesize that, relative to educational modules, mobile video interpreting will be more cost-effective (*H4a*) per additional interpreted clinic visit and (*H4b*) per additional instance of patient comprehension.

The estimated incremental cost-effectiveness ratios (ICER) will provide evidence of the resources required to increase interpreted clinic visits and improve patient comprehension [111]. Our goal is to support decision-making about which strategy healthcare organization leaders may choose to implement, and thus, we will estimate ICERs from the organization perspective.

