Effectiveness measures will be based on Aim 1 analyses; cost data will come from two sources. The first source is administrative, including vendor invoices and budgets for payroll. Costs that cannot be determined will be estimated with a micro-costing approach in which unit cost multipliers are applied to the quantity of each type of service or resource utilized; examples include the use of shared resources (space, office equipment) and opportunity costs experienced by clinic staff. All cost data are summed to obtain total costs [112], using an approach we have used previously [113, 114]. While mobile video interpreting-assigned providers may also have used other professional interpretation, we will assign mobile video interpreting-related costs to the mobile video interpreting and combination groups and nonmobile video interpreting interpreter costs (which would not be necessary if a clinic used mobile video interpreting only) to the education group. Interpreter costs will be based on actual usage from vendor invoices, attributed to assigned group. Education module development will be annuitized over the study period. Time costs for providers (time on modules, learning to use mobile video interpreting) and study staff (reminder emails, mobile video interpreting support) will be estimated using the mean hourly wage from the National Compensation Survey, plus fringe rates from the Bureau of Labor Statistics Employer Costs for Employee Compensation. Provider costs due to own-device use for mobile video interpreting will be estimated with hardware depreciation allowances per the US Internal Revenue Code. Costs will be inflation-adjusted to common-year dollars using the Personal Health Care Expenditure Deflator or Personal Consumption Expenditure price index [112].

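### Module development is written off over the study period rather than its useful life, which favours video in the video-versus-education ICER; separately, providers' own-device costs are summed into an organisation-perspective total

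*Protocol article*

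**What the plan says.** In Data analysis, Aim 3, the protocol article fixes the perspective: "we will estimate ICERs from the organization perspective". The stated purpose is to help leaders of healthcare organisations choose a strategy. H4a and H4b expect video to be more cost-effective than education, per additional interpreted visit and per additional instance of comprehension. Each is tested in two contrasts: (i) video against education, and (ii) video plus education against education. Total cost per strategy is the sum of the cost items listed.

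Two rules for those items matter here.

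- **Development.** "Education module development will be annuitized over the study period". Under Cost data, the list of administrative costs ends with "wireless Internet; and educational module development, following recommendations for economic analysis in implementation science". The section Web-based educational modules says that, with a university group, "we transformed the workshops into interactive web-based modules", and that these were pilot tested and revised. Table 2 gives providers continuing access, and the Discussion calls both strategies scalable.
- **Own devices.** "Provider costs due to own-device use for mobile video interpreting will be estimated with hardware depreciation allowances". Under Cost data, the final provider survey also collects "excess data charges associated with mobile video interpreting use (if any), and wear or damage to personal devices".

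**The concern.** Annuitising spreads a one-off outlay over the years in which the asset is used. The study period is a research timetable. Using it as the asset's life gives the modules no value after the trial, which does not fit the article's description of a finished product meant for wider use. Education is the comparator in contrast (i), so a heavier fixed charge on it shrinks the video-minus-education cost difference. The costing rule then moves the ratio towards H4 whatever the data show.

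The own-device rule is a different problem. Depreciation, data charges and wear on a provider's personal phone are not costs to the organisation unless it reimburses them, and the article does not say that it would. It does give such a reason for counting study-team time (clinic staff would do that work in practice), but none for personal devices.

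At stake is the ICER offered to decision-makers. The primary outcome is not affected.

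**Working it through.** **1. Is there a figure to reproduce?** The article gives no development cost, discount rate, useful life or ICER, so no Aim 3 figure can be checked. The visit numbers used for scaling in step 5 do reproduce: (55 − 9) providers × 7 visits × 18 months = 5,796, and 5,796 / 3 = 1,932 per group, as stated under Interpreter use.

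**2. Inputs.** Effectiveness comes from phases 1 and 2, which is 18 months; phase 3 brings the total to 27 months. The article does not define the study period for costing, so both lengths are tried as the asset's life. The lives of 5 and 10 years and the discount rates are assumptions.

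**3. Formula.** For development cost D, rate r and life L in years, the annual charge is D × r / (1 − (1 + r)^−L), or D / L when r = 0. The share charged in the 18-month window is the annual charge × 1.5 / D.

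At r = 3% the annual charge is 0.692 D (L = 1.5), 0.466 D (L = 2.25), 0.218 D (L = 5) and 0.117 D (L = 10).

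| Life | r = 0% | r = 3% | r = 5% |
|---|---|---|---|
| 18 months | 100% | 104% | 106% |
| 27 months | 67% | 70% | 72% |
| 5 years (assumed) | 30% | 33% | 35% |
| 10 years (assumed) | 15% | 18% | 19% |

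At 3%, the study-period rule charges between 69.9 / 32.8 = 2.1 times and 103.8 / 17.6 = 5.9 times what the longer lives would.

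**4. Different costing window.** If costs are accumulated over 27 months with a 27-month life, the share at 3% is 105%, against 49% for a 5-year life (0.218 × 2.25). The ratio is again about 2.1.

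**5. Effect on the ICER in contrast (i).** At the 5-point difference used for sample size, video yields 0.05 × 1,932 = 96.6 more interpreted visits. The ICER falls by (share × D) / 96.6. At 3% this is 0.72% of D (27-month life) to 1.07% of D (18-month life) per extra interpreted visit, against 0.34% (5 years) and 0.18% (10 years).

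**6. Contrast (ii).** Both groups receive education. If development is charged equally to each, it drops out of the cost difference.

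**7. Own-device items.** Video-related costs are assigned to the video and combination groups. These items therefore raise the incremental cost in both contrasts, opposite in direction to the development rule in contrast (i).

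**The case against.** The strongest reply is that useful life and discount rate are details that an article leaves to the full plan, that the cost list follows published recommendations, and that Aim 3 is secondary. This would succeed if the article were silent on the horizon. It is not: it names the study period.

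Other parts of the reply stand and limit the point.

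- A reader might infer that development is always charged in full. That requires the costing window to equal the study period. With a 27-month life and costs matched to 18 months, the share is about 70%.
- A reader might infer that an adopting organisation would pay nothing for the modules. The article shows that they are built, but gives no licence or access terms. Excluding development is therefore a sensitivity case rather than the obvious base case.
- A reader might argue that the strategies are treated unequally because app development is buried in vendor prices. The article says nothing about how vendors price their apps.
- A reader might take the supplied phones and "an extra charger, shock-resistant case, disposable antimicrobial sleeves, and a positioning stand" as missing from the costing. Aim 3 assigns video-related costs to the video groups and micro-costs resources used, with an open list of examples, and Cost data includes interpreter-specific hardware. The supplies can fit there.
- Own-device depreciation could stand in for equipment that an organisation would provide, since providers may use a study-issued phone instead. That reading is defensible, but the article does not state it.

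**Conclusion.** The point holds in limited form. The stated development rule overcharges education in contrast (i), by about 2 to 6 times at 3% relative to assumed lives of 5 to 10 years, and so works towards H4 there. It largely cancels in contrast (ii). The own-device items conflict with the stated perspective as written and work against video.

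It would be tempting to conclude that the costing as a whole is biased in favour of H4. The documents do not support that: the two problems push in opposite directions in contrast (i), and without any cost figures the net effect can be neither signed nor sized. The multiples rest on the assumed lives; changing the rate between 0% and 5% matters little. The matter is still more than missing detail, because a fixed rule alters the ratio that decision-makers will be given.

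**What to change.** In Data analysis, Aim 3:

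1. Annuitise module development over a stated useful life in the base case, with the discount rate given and the costing window defined. Report sensitivity ICERs under the study-period rule and with development excluded as sunk.
2. Report provider-borne device depreciation, data charges and wear outside the organisation-perspective total. Alternatively, state that the organisation would reimburse them and show the ICER with and without them.

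The cost is a few sentences and one scenario table. No new data collection is needed. The drawback is that a useful life must be assumed, so it has to be varied over a plausible range.

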We will calculate total costs associated with each implementation strategy by summing the above costs. To test *H4a*, we will calculate the ICER for each additional interpreted clinic visit, by calculating the difference in total costs for (i) mobile video interpreting vs education and (ii) mobile video interpreting plus education vs education, and then divide by the difference in number of professionally interpreted visits for providers assigned to (i) mobile video interpreting vs education and (ii) mobile video interpreting plus education vs education. To test *H4b*, we will calculate the ICER for each additional instance of patient comprehension. To do so, we will calculate the difference in total costs for (i) mobile video interpreting vs education and (ii) mobile video interpreting plus education vs education and then divide by the difference in proportion of patients who correctly reported their diagnosis for providers assigned to (i) mobile video interpreting vs education and (ii) mobile video interpreting plus education vs education.

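### Aim 3 names a point ICER as the test of H4a and H4b, without saying what result would support the claim that mobile video interpreting is more cost-effective

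*Protocol article*

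**What the plan says.** All of this is in the Aim 3 part of the Data analysis section of the protocol article.

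- **Hypothesis.** It is comparative and directional: "relative to educational modules, mobile video interpreting will be more cost-effective", stated per additional interpreted visit (H4a) and per additional instance of comprehension (H4b).
- **Purpose.** The ICERs "will provide evidence of the resources required to increase interpreted clinic visits and improve patient comprehension". The section adds: "Our goal is to support decision-making about which strategy healthcare organization leaders may choose to implement".
- **Test of H4a.** "we will calculate the ICER for each additional interpreted clinic visit": take the difference in total costs, then "divide by the difference in number of professionally interpreted visits for providers assigned to" each strategy. The contrasts are mobile video versus education, and both strategies versus education.
- **Test of H4b.** "we will calculate the ICER for each additional instance of patient comprehension": take the same cost differences, then "divide by the difference in proportion of patients who correctly reported their diagnosis".
- **Source of the effects.** "Effectiveness measures will be based on Aim 1 analyses".

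Both procedures are introduced as tests of their hypotheses. The section gives no criterion for being more cost-effective: no dominance rule, no willingness-to-pay value or range, and no interval.

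**The concern.** A hypothesis test needs a result that would count for the hypothesis and one that would count against it. A single ratio supplies neither when one strategy is both dearer and more effective. The answer then depends on what an organization would pay for an extra interpreted visit or an extra patient who understands the diagnosis, and the article gives no such value. When one strategy is cheaper and better, the direction is clear, but nothing in the procedure says how firmly the data support it.

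Aim 3 is meant to help organization leaders choose a strategy. The denominator of each ratio is an Aim 1 difference estimated from about 46 providers. If it is imprecise, the ratio can be far from the truth or have the wrong sign, and the ratio alone would not show this.

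**Working it through.** **1. The plan's own figures reproduce.** None is given for H4a or H4b. The nearest are those for the Aim 1 outcomes that supply the denominators.

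- Providers after loss: 55 − 9 = 46. Visits: 46 × 7 per month × 18 months = 5796, and 5796/3 = 1932 per group, as stated.
- Power for 5 points with 1932 independent visits per group (two-sided 5% level assumed): 0.875 at its lowest (47.5% v 52.5%). The article says above 80%.
- Power for 14 points with 216 surveys per group: 0.831 at its lowest (43% v 57%). The article says at least 80%.

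**2. What a point ICER can decide.** Let ΔC and ΔE be the cost and effect differences, video minus education, and λ the willingness to pay. Video is more cost-effective when λ·ΔE − ΔC > 0.

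| ΔE | ΔC | ICER sign | More cost-effective |
|---|---|---|---|
| + | − | negative | video, for any λ |
| − | + | negative | education, for any λ |
| + | + | positive | video only if λ > ICER |
| − | − | positive | video only if λ < ICER |

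The two trade-off rows need a λ that the article does not give. The two dominance rows are settled in direction by the separate differences, not by the ratio.

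**3. Spread of the ratio from the denominator alone.** Hold ΔC fixed and take a Wald 95% interval for ΔE with independent observations. The base rates are assumed.

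- H4a, 47.5% v 52.5%, 1932 per group: SE = √(2 × 0.475 × 0.525/1932) = 1.61 points, so the interval is 1.9 to 8.1 points. The ICER runs from 0.61 to 2.7 times its point value.
- H4b, 50% v 64%, 216 per group: SE = √((0.25 + 0.64 × 0.36)/216) = 4.72 points, so the interval is 4.8 to 23.2 points. The ICER runs from 0.60 to 2.9 times its point value.

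That is a four- to fivefold range at differences the study is powered to detect, before clustering or cost uncertainty.

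**4. Chance of a zero or negative denominator (H4a only).** Assumptions: true difference 5 points, mean use 50%, latent-scale provider ICC 0.05, 0.10 or 0.20, equal visit volume in both groups, and no gain from stratification.

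- Provider variance on the logit scale = ICC/(1 − ICC) × π²/3 = 0.17, 0.37, 0.82. On the proportion scale this gives provider SDs of 0.10, 0.14 and 0.19.
- Providers per group: k = 46/2 = 23, or 46/3 ≈ 15. Visits per provider: n = 7 × 18 = 126, or 7 × 9 = 63 for one phase.
- SE = √(2 × (SD²/k + 0.25/(k·n))), and P = Φ(−5/SE) with SE in points.

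| k | n | SE in points (ICC 0.05, 0.10, 0.20) | P(estimate ≤ 0) |
|---|---|---|---|
| 23 | 126 | 3.2, 4.3, 5.8 | 6%, 12%, 19% |
| 23 | 63 | 3.5, 4.5, 5.9 | 8%, 13%, 20% |
| 15 | 126 | 4.0, 5.4, 7.1 | 11%, 18%, 24% |
| 15 | 63 | 4.3, 5.6, 7.3 | 12%, 19%, 25% |

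**5. Effect of stratification.** Randomization is stratified by baseline use and clinic. Suppose this removed the provider variance explained by a baseline-to-follow-up correlation r, so that SD² becomes SD²(1 − r²). With k = 23 and n = 126, the range of 6–19% becomes 4–16% for r = 0.5 and 1–8% for r = 0.8. Both values of r are assumptions.

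**The case against.** The strongest reply is that this is a condensed article. Bootstrap intervals, acceptability curves and willingness-to-pay ranges are commonly left to a fuller plan, and none is shown here. That stands. A reader might infer that the trial will report Aim 3 with no uncertainty at all; the text does not say so, and silence on those details is not the point made here. The point is what the article does state: calculating a ratio is named as the test of a directional hypothesis.

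A reader might also infer that the plan can never say which strategy is more cost-effective. That goes too far. The cost and effect differences are calculated before they are divided, so their signs are known and dominance is visible in direction.

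Nor is it right that nothing reported would reveal a chance result. Aim 1 gives 95% intervals on the odds ratios for interpreter use and comprehension. They would warn of a weak denominator, but they are not on the scale of the ICER's differences and carry no cost uncertainty.

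Finally, the 5 points is a difference the study is powered to detect. The article does not call it the expected effect, so the probabilities in the working are not forecasts.

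It can also be argued that each organization should set its own value on an extra interpreted visit. That fits the stated goal, and it favors presenting Aim 3 as estimation. It does not turn a point ratio into a test.

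**Conclusion.** The concern holds in this form: Aim 3 presents a point ICER as the test of H4a and H4b without stating what result would support them. In the trade-off quadrants the ratio gives no answer without a willingness-to-pay value. In the dominance quadrants it gives a direction without confidence.

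The size can only be illustrated, since the article gives no costs, no threshold, no base rate and no ICC. For H4a at a true 5-point difference, the estimated difference would be zero or negative about 6–20% of the time with 23 providers per group and 11–25% with 15. This rests on the assumed 50% mean and ICC of 0.05 to 0.20 and ignores stratification, which would lower it. It describes the denominator only; the sign of the ICER also depends on the cost difference. No such probability was worked out for H4b. The point affects the third aim and leaves the primary comparison untouched.

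**What to change.** In the Aim 3 text, assess H4a and H4b by incremental net benefit per visit: willingness to pay × effect difference − cost difference, over a stated range of values. Take 95% intervals from a bootstrap that resamples providers within assigned strategy and carries the SMART weights. Report the ICER alongside, with its cost and effect differences, so that the quadrant is visible.

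Working per visit also puts costs and effects on one scale. At present H4b is worded per instance of comprehension but divides total cost by a difference in proportions.

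Alternatively, stop calling the calculation a test and present Aim 3 as estimation, with the same intervals.

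The cost is some rewording and a little more analysis on data the study already plans to hold. The conclusion may be less decisive than a single ratio.

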#### Aim 1: Compare the effectiveness of two implementation strategies, alone and in combination, to improve use of interpretation and comprehension for patients/parents with language barriers seen in adult/pediatric primary care settings

We hypothesize that, compared to educational modules, provider access to mobile video interpreting will lead to (*H1*) greater odds of interpreter use for visits with patients/parents with language barriers (primary outcome) and (*H2*) better comprehension among patients/parents with language barriers. We also hypothesize (*H3*) that mobile video interpreting and educational modules together will yield greater odds of interpreter use than either strategy alone.

To test *H1* and *H3*, we will use assigned strategy and data collected during phases 1 and 2. Under the SMART design, comparisons of first-stage interventions, comparisons of second-stage interventions, and comparisons of the adaptive intervention with both stages can be conducted simultaneously using standard software with a technique called a “weighted and replicated” regression approach, using weighted generalized estimating equations (GEE) [66, 97]. Weighted GEE allows us to work with binary outcomes and weights and adjust for clustering within providers. Within-clinic correlations will be assessed by including clinic-specific random effects in our regression models and estimating the intra-cluster correlation coefficients. Significance of the intra-cluster correlation coefficients will be examined by comparing models with and without clinic-specific random effects using likelihood ratio tests. If no strong within-clinic correlation is detected, we will use fixed-effects regression models for their better power; otherwise, estimates and inference based on random-effects regression models will be reported. *H1* and *H3* will be tested using the Wald test and robust standard error estimates [66, 97]. Model-based estimates of odds ratio comparing education to mobile video interpreting or both will be reported, along with 95% confidence intervals [98].

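### Aim 3 plans both cost-effectiveness ratios against education; the step from mobile video to the combination is neither planned nor reported, so ratio (ii) alone can mislead a three-way choice

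*Protocol article*

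**What the plan says.** Under Data analysis, Aim 3, the heading sets the scope as the incremental cost-effectiveness "of each implementation strategy (mobile video interpreting, education, and both"). The purpose is stated there too: "Our goal is to support decision-making about which strategy healthcare organization leaders may choose to implement".

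The hypotheses are narrower. H4a and H4b say only that, "relative to educational modules, mobile video interpreting will be more cost-effective", per additional interpreted visit and per additional instance of comprehension.

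For the calculation, the section first says "We will calculate total costs associated with each implementation strategy by summing the above costs". It then names the cost contrasts as "i) mobile video interpreting vs education and (ii) mobile video interpreting plus education vs education". For H4a the analysts "divide by the difference in number of professionally interpreted visits for providers assigned to" the same two contrasts. For H4b they "divide by the difference in proportion of patients who correctly reported their diagnosis", again for the same two contrasts. Education is the comparator throughout.

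Under Aim 1, H3 compares the combination with both single strategies: "mobile video interpreting and educational modules together will yield greater odds of interpreter use than either strategy alone". Mobile video alone is thus a comparator for effect but not for cost-effectiveness.

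**The concern.** With three mutually exclusive options, the useful incremental ratio compares each option with the next less effective one that is still a reasonable choice. A common comparator for every option does not do this. If the combination is judged only against education, its ratio mixes two steps: from education to video, and from video to both. A strong first step can hide a weak second one.

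At stake is the decision that Aim 3 says it serves. An organization that has mobile video, or would choose it, needs the extra cost per extra interpreted visit of adding education. The Discussion makes this a live question: it expects that one strategy may be enough for many providers and invokes the minimum intervention needed for change. The design also produces the comparison. Under Study design and randomization, lower-use providers in the video arm are re-randomized to continue or to add education.

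**Working it through.** The protocol gives no cost or ratio, so there is no stated figure to reproduce. The check is algebra followed by illustration.

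**Algebra.** Write C for total cost and E for effect, with subscripts E (education), V (video) and B (both).

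- Ratio (i) = (C_V − C_E)/(E_V − E_E)
- Ratio (ii) = (C_B − C_E)/(E_B − E_E)
- Unplanned ratio (iii) = (C_B − C_V)/(E_B − E_V)

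Education cancels on subtraction: C_B − C_V = (C_B − C_E) − (C_V − C_E), and likewise for effect. So (iii) follows exactly, as a point estimate, from the planned totals and differences.

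When both effect steps are positive, (ii) is the average of (i) and (iii) weighted by the effect gained in each step. It therefore lies between them:

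- If (iii) is larger than (i), ratio (ii) understates the cost of the added step.
- If (iii) is smaller than (i), video is extendedly dominated, and education is the right comparator for the combination.

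**Illustration 1 (all inputs assumed, per 100 visits).** Education: 50 interpreted at cost 1,000. Video: 60 at 1,500. Both: 62 at 2,300.

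- (ii) = (2,300 − 1,000)/(62 − 50) = 1,300/12 = 108
- (iii) = (2,300 − 1,500)/(62 − 60) = 800/2 = 400, about 3.7 times as large

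**Illustration 2.** The 1,932 visits per group come from the Interpreter use section. The rest is assumed: total costs 60,000 (education), 80,000 (video) and 95,000 (both), with 50% interpreted under education and 55% under video. Then (i) = 20,000/(1,932 × 0.05) = 20,000/96.6 = 207. The share under both is varied:

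| Interpreted under both | Gain over education | (ii) = 35,000/gain | Gain over video | (iii) = 15,000/gain |
|---|---|---|---|---|
| 60% | 193.2 | 181 | 96.6 | 155 |
| 57% | 135.2 | 259 | 38.6 | 388 |
| 55.5% | 106.3 | 329 | 9.7 | 1,553 |
| 55% | 96.6 | 362 | 0 | undefined, no gain |
| 54% | 77.3 | 453 | −19.3 | dominated by video |

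The cost of adding education to video is 35,000 − 20,000 = 15,000 in every row, equal to 95,000 − 80,000 directly. The averaging also checks at 57%: (96.6 × 207.0 + 38.64 × 388.2)/135.24 = 259.

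In the last two rows (ii) remains a finite positive number, although the added education buys nothing or the combination is worse and dearer than video.

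**If only the two ratios were published.** With s the combination's gain divided by video's gain, (iii) = (s × (ii) − (i))/(s − 1). Ratios of 207.0 and 258.8 then fit (iii) = 777, 362, 311 or 276 for s = 1.1, 1.5, 2 or 4. The ratios alone do not identify the increment; the totals do.

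**The case against.** The best defence is that the planned contrasts match the stated hypotheses. H4a and H4b concern video against education, and contrast (i) tests them in full. That stands: no hypothesis goes untested. But contrast (ii) is not needed for H4a or H4b. It serves Aim 3's wider scope, which includes both strategies together, and for that purpose it is not enough on its own.

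A second defence is that dominance rules are detail that an article leaves to the full economic plan. This has some force for the procedure. It has less for the comparators, which the article names explicitly and identically for H4a and H4b.

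Three stronger readings are tempting, and the documents do not support them.

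- A reader might infer that the cost of adding education to video cannot be recovered. It can, because total costs are calculated for each strategy and both differences share one comparator. What is missing is the commitment to report it. Its uncertainty would also need the joint data.
- A reader might infer from H1, H3 and H4 that video must be the combination's comparator and that (ii) always flatters it. Those hypotheses order effects and compare video with education; none fixes the combination's cost per gain. In the 60% row H1 and H3 hold on the point estimates, video is extendedly dominated, and (ii) is the right figure.
- A reader might infer that the design randomizes only the video-to-both step, so (ii) should be demoted. In fact lower-use providers in both first-stage arms are re-randomized, so adding video to education is tested too. In each arm the top tertile is not re-randomized.

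**Conclusion.** The concern holds as a gap in what Aim 3 plans to compare and report. The combination is evaluated only against education, and relying on (ii) for a three-way choice can mislead, because (ii) includes video's own gain. Contrasts (i) and (ii) correctly answer the pairwise questions they name.

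Neither the size nor the direction can be given from the documents. The figures 108 against 400 and 181 against 155 rest on assumed costs and shares and show only that the gap can be large and can go either way. The algebraic results rest on no figures; the averaging result needs positive effect gains at both steps.

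This bears on the economic aim and the decision it is meant to inform. It does not touch the primary outcome or the tests of H1 to H3. It is worth correcting because the correction is cheap.

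**What to change.** In Data analysis, Aim 3, add contrast (iii), mobile video plus education versus mobile video, for both H4a and H4b. Then state that the three strategies will be ordered by effect and checked for dominance and extended dominance, and that each remaining strategy's ratio will be reported against the next less effective one that remains. Report the cost and effect totals per strategy beside the ratios, so that readers can check any step.

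Keep (i) and (ii) as planned pairwise contrasts: (i) addresses H4a and H4b, and (ii) is the correct comparison if video proves dominated or extendedly dominated.

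The cost is a sentence or two of text and slightly more analysis, with no new data. The combination may look more or less favourable as a result.
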